## Abstract

**Introduction:**

Chronic migraine (CM) is a prevalent neurovascular disorder that significantly affects quality of life. Research has shown promising results for the efficacy of acupuncture in the treatment of chronic migraine. This study aims to evaluate the efficacy of acupuncture as a prophylactic treatment for chronic migraine through a multicenter randomized controlled trial.

**Materials and methods:**

This investigation constitutes a prospective, two-arm, multicenter randomized controlled trial involving a total of 180 patients diagnosed with chronic migraine (CM). Participants will be allocated in a 2:1 ratio to either the treatment group, receiving acupuncture, or the control group, receiving sham acupuncture. The intervention will be administered three times per week over a 6-week treatment period, followed by an 8-week follow-up phase. The primary outcome measure is the change from baseline in the average number of monthly headache days during weeks 3–6 of the treatment period. Secondary outcomes include changes in monthly headache days during follow-up, acute medication use days (AMDs), Migraine-Specific Quality of Life (MSQ), headache symptom scores, and pain severity as assessed using the visual analog scale (VAS).

**Ethics and dissemination:**

The study was approved by the Ethics Committee of Shandong University of Traditional Chinese Medicine (approval number: 2024-014-01-KY) and is registered with the Chinese Clinical Trial Registry (registration number: ChiCTR2400084720). Written informed consent was obtained from all participants. The results will be disseminated through peer-reviewed publications and conference presentations.

**Clinical trial registration:**

https://www.chictr.org.cn/showproj.html?proj=226947, identifier ChiCTR2400084720.

## Introduction

Migraine is a neurovascular disorder that affects approximately 15.2% of the global population. It ranks as the second leading cause of health loss in terms of years lived with disability worldwide and is the leading cause among women aged 15–49 years (1). Chronic migraine (CM), defined by the International Classification of Headache Disorders, 3rd edition (ICHD-3), as experiencing headaches occurring on ≥15 days per month for >3 months with at least 8 days per month fulfilling criteria for migraine, represents the most severe form of migraine and affects approximately 1–3% of the general population (2). Compared to those with episodic migraine, patients with chronic migraine have a higher prevalence of depression and anxiety, dyspepsia, irritable bowel syndrome, epilepsy, chronic sinusitis, and many other disorders (3). Current pharmacological treatments for CM include oral medications such as topiramate, valproate, propranolol, and injectable botulinum toxin A (BoNT-A), as well as recently developed monoclonal antibodies targeting the calcitonin gene-related peptide (CGRP) pathway (4, 5). However, these pharmacological treatments may cause adverse events (AEs) such as hypotension, depression, somnolence, and gastrointestinal intolerance (6). These comorbidities and adverse events not only impose a greater burden on patients but also significantly impair their health-related quality of life, negatively affecting treatment response, medication adherence, and overall wellbeing (7). Therefore, the effective management of chronic migraine requires a comprehensive strategy that not only focuses on ameliorating headache symptoms but also prioritizes improving medication adherence, emphasizing daily disease management, and ultimately enhancing the patient’s overall quality of life.

Acupuncture, a non-pharmacological therapy with a long history in Traditional Chinese Medicine, is increasingly recognized globally for its favorable safety profile and low incidence of adverse events (8, 9). Multiple high-quality systematic reviews (10, 11) and randomized controlled trials (RCTs) (12, 13) have consistently established the effectiveness of acupuncture as a prophylactic treatment for migraine, demonstrating significant long-term reductions in headache frequency and severity in the general migraine population. However, the majority of existing high-quality clinical studies have primarily focused on patients with episodic migraine, while dedicated research targeting patients with chronic migraine (CM), who experience more severe symptoms and greater management complexity, remains relatively limited (14). CM patients experience a significantly higher disease burden compared to EM patients (15), and the effective management of CM should adopt a comprehensive strategy that not only alleviates pain symptoms but also prioritizes improving medication adherence, managing the associated emotional burden, and ultimately enhancing the patient’s overall health-related quality of life (16).

Therefore, the present study is designed to rigorously evaluate acupuncture as a prophylactic treatment for chronic migraine using a multicenter randomized controlled trial. It is hypothesized that patients who receive acupuncture will demonstrate significantly greater reductions in monthly headache days, improved migraine-specific quality of life, and reduced acute medication use compared to those who receive sham acupuncture.

## Materials and methods

### Study design

This study is a prospective, two-arm, multicenter, randomized controlled trial. A total of 180 patients with chronic migraine will be allocated in a 2:1 ratio to a treatment or control group. The trial will consist of 6 weeks of acupuncture or sham acupuncture treatment, followed by an 8-week follow-up period. The study centers are the Affiliated Hospital of Shandong University of Traditional Chinese Medicine, Yantai Traditional Chinese Medicine Hospital, and Shandong Provincial Third Hospital. Patient recruitment has been ongoing since May 2024, and the timeline for all patients to complete the assessment is shown in Figure 1. The study flowchart is shown in Figure 2. The protocol adheres to the principles of the Declaration of Helsinki and will be reported in accordance with the Standard Protocol Items: Recommendations for Interventional Trials guidelines (Supplementary File S1).

**Figure 1 fig1:**
[figure not shown]
Timeline for all patients to complete assessments.

**Figure 2 fig2:**
[figure not shown]
Study flowchart.

### Recruitment

Participants are being recruited from individuals diagnosed with chronic migraine according to the criteria established by the International Headache Society (IHS). Recruitment is taking place across the three previously designated medical centers. Recruitment advertisements have been published through posters and social media to attract potential participants. Clinicians will determine in person whether patients meet the strict inclusion and exclusion criteria for the study. Patients who meet the criteria and volunteer to participate will sign a written informed consent form before the start of the study. They will be fully informed of the study details, including procedures, potential benefits, and risks, with the exception of specific information regarding the needling site. Participants will be free to withdraw from the study at any time without any negative impact on their future medical treatment. In addition, measures will be taken to ensure the confidentiality of participants’ data.

### Inclusion criteria

Patients who meet the diagnostic criteria for chronic migraine according to the 2018 International Classification of Headache Disorders (3rd edition) (ICHD-3) (2).Patients aged 18–65 years.Patients who have not received acupuncture treatment in the past 3 months;Patients who voluntarily agree to participate and sign the informed consent form.

### Exclusion criteria

Individuals prone to concurrent infections and bleeding, lactating women, pregnant women, and individuals with allergies (especially those allergic to metal needles).Individuals with serious systemic diseases, such as heart, liver, kidney, or brain disorders.Individuals with mental or somatic disorders who are unable to independently complete the clinical study.Individuals who have taken migraine prevention drugs, anti-anxiety medications, or antidepressants within the past month of the study.Individuals who are unable to cooperate with the treatment and complete follow-up or those who are currently participating in other relevant clinical trials.

### Randomization and allocation concealment

Participants in this study are strictly being screened according to the diagnostic, inclusion, and exclusion criteria. A random number list was generated using SPSS 25.0 software and converted into random number cards. Participants will be randomly allocated into two groups in a 2:1 ratio: 120 participants in the acupuncture treatment group and 60 of them in the control group. The allocation process will be kept confidential using sealed, opaque envelopes. The random number cards will be placed inside these envelopes, which will be numbered sequentially. The envelopes will be opened in the order in which the participants enter the study, and the participants will be assigned to their respective groups based on the number inside the envelope, ensuring a 2:1 allocation ratio between the groups.

### Blinding

Due to the specific nature of acupuncture, it is not feasible to blind practitioners. Therefore, blinding will be implemented for the participants, evaluators, and statisticians. Practitioners adhere to strict confidentiality protocols to avoid disclosing group allocation to the participants and evaluators. Evaluators are responsible for collecting and analyzing the data unrelated to the treatment process and are not exposed to any information about group allocation throughout the study. Statisticians are solely responsible for data analysis and are not involved in the treatment process, thereby ensuring the objectivity and impartiality of the results.

To evaluate participant blinding integrity, Bang’s Blinding Index (BI) will be calculated at the completion of the treatment phase (17). After the final treatment session, the participants will be asked to guess their group allocation (real acupuncture, sham acupuncture, or unsure) and to rate their confidence in this guess.

The Credibility/Expectancy Questionnaire (CEQ) (18) will be administered after the first treatment session. Group differences in the CEQ scores will be examined to verify that expectancy was balanced between the groups.

After the completion of statistical analysis, the unblinding procedure will be initiated. Researchers responsible for unblinding will disclose group information to the data analysts as necessary to finalize comparisons and interpret the study results.

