### Outcome measures

#### Primary outcome measures

The primary outcome measure is the change from baseline in the average number of monthly headache days during weeks 3–6 of the 6-week treatment period.

According to the headache diary, patients will be asked about the duration of headache, defined as the number of days on which the headache lasted for at least 4 h. Headaches will be considered according to the ICHD-III criteria: criteria C and D (1.1) for migraine without aura, criteria B and C (1.2) for migraine with aura, or criteria 1.6 for possible migraines. Patients will also be required to record, on days with a migraine or headache, successful treatment with trastum, ergot, or other migraine-specific acute drugs.

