### Data management

All personnel involved in data management, including data collectors, data managers, and statisticians, will receive training to ensure adherence to the study’s data management protocols. Each participant’s CRF will be meticulously completed by the investigator based on the participant’s hospital records and original observation notes. Data entry will be conducted using the EpiData 3.1 software with a double-entry system by independent data entry personnel. The data manager, in collaboration with the principal investigator, will define the range and logical checks for the data and program these into the system to prevent errors. Any discrepancies found during data entry or validation will be documented and corrected, with records of the errors and corrections maintained.

All data, including paper CRFs and electronic files, will be securely stored. Paper records will be archived in a designated order and stored in a secure location, and electronic documents will be securely stored on a passwordprotected computer. These records will be preserved for at least 5 years following publication, in accordance with national regulations on clinical trial data management.

The Ethics Committee will periodically review the trial’s progress, monitoring data collection, allocation, and security. A formal data monitoring committee (DMC) will not be established. This decision is justified by the low-risk nature of the interventions (acupuncture and sham acupuncture) when performed by certified practitioners, the relatively short duration of the treatment phase (6 weeks), and the fact that no formal interim analyses for efficacy are planned. Instead, safety monitoring responsibilities will be jointly handled by the principal investigators and the Ethics Committee, which will conduct periodic reviews of safety data (including all AEs and SAEs) in addition to its standard oversight of trial conduct.

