### Quality control

The acupuncture procedure will primarily be carried out by acupuncture specialists with more than 10 years of clinical experience. A launch meeting has been convened before the formal initiation of the trial to provide training on the purpose and design of the trial, treatment strategies, and quality control for all staff. The clinical participants will be required to complete the CRFs according to the design requirements, filling them in carefully and in detail. The study medical records and the CRFs shall be the original records and shall not be altered. All data in the clinical trial should be recorded, and the original report (or copy) should be attached to the case report form. Data that are significantly high or outside the clinically acceptable range will be verified, and necessary explanations will be provided by the physicians participating in the clinical trial. Clinical supervisors make regular on-site visits to research centers, check original information on a sample basis, hold regular meetings on specific issues, and provide timely feedback in the form of supervision reports and subject briefings to improve the quality of supervision.

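### With a fixed 120:60 split, group size identifies the acupuncture arm, so holding back group identity until the analysis is complete does not blind the statistician

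*Protocol article*

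**What the plan says.** The Blinding section of the protocol article accepts that practitioners cannot be blinded and states that "blinding will be implemented for the participants, evaluators, and statisticians". For statisticians it gives one measure, separation of roles: "Statisticians are solely responsible for data analysis and are not involved in the treatment process". It then places unblinding after the statistical analysis has been completed. The next sentence has group information passed to the analysts, where needed, so that they can complete the comparisons and interpret the results.

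The section on randomisation and allocation concealment fixes a 2:1 ratio, with "120 participants in the acupuncture treatment group and 60 of them in the control group". The sample size section gives the same totals and a predicted dropout of 10%.

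The Data analysis section leaves some choices to be settled on the data. The t-test or the Mann–Whitney test is used according to a normality test. The per-protocol set depends, among other things, on good compliance. Further analyses may be added, with details left to a statistical analysis plan that is not shown.

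For evaluators, the Blinding section says that they "are not exposed to any information about group allocation throughout the study".

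**The concern.** Blinding a statistician by withholding group identity works only if the data do not give the identity away. The analysis compares two groups and is to be finished before unblinding, so the statistician must hold some group code while doing it. Under equal allocation, neutral labels leave real doubt about which group is which. Under 2:1 allocation they leave almost none, because the first table of group sizes settles it.

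At stake is a property that the trial states and will presumably report. If the arms can be identified throughout the analysis, the data-dependent choices in the Data analysis section are not protected by blinding. They are protected only to the extent that they are fixed in advance. The sentence on passing group information to the analysts adds to the difficulty, since it allows comparisons to be completed after the blind is broken.

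**Working it through.** **Inputs from the protocol article.** Arm sizes are 120 and 60 (randomisation section). The sample size section gives reductions of 3.9 ± 3.0 and 2.2 ± 3.2 days, α = 0.05, power 0.90, ratio 2:1, an evaluable requirement of 107 + 54, and 10% dropout. Sidedness is not stated, so two-sided is assumed. Dropout rates other than 10% are assumptions used to show a range.

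**Step 1: reproduce the planned sizes.** With difference Δ = 3.9 − 2.2 = 1.7 and unequal SDs,

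n(sham) = (SD_sham² + SD_acu²/2) × ((z₀.₉₇₅ + z₀.₉₀)/Δ)²

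= (10.24 + 4.50) × ((1.960 + 1.282)/1.7)² = 14.74 × 3.636 = 53.59, so 54.

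Acupuncture: 2 × 53.59 = 107.18, or about 107. For dropout, 107/0.9 = 118.9 (119) and 54/0.9 = 60. The stated 107 + 54 reproduces, and 120 + 60 is in line with it.

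**Step 2: how often does size alone identify the arm?** Let A ~ Bin(120, 1 − d_acu) and S ~ Bin(60, 1 − d_sham) be the numbers analysed. The probability that the larger group is acupuncture is

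P(A > S) = Σₓ P(A = x) × P(S ≤ x − 1).

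| Loss, acupuncture | Loss, sham | Expected sizes | P(larger group is acupuncture) |
|---|---|---|---|
| 0% | 0% | 120 : 60 | 1 |
| 10% | 10% | 108 : 54 | above 0.9999 |
| 20% | 20% | 96 : 48 | above 0.9999 |
| 20% | 0% | 96 : 60 | above 0.9999 |
| 30% | 0% | 84 : 60 | above 0.9999 |
| 40% | 0% | 72 : 60 | 0.983 |

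Fixed totals are not essential. If 180 participants were simply randomised 2:1, P(Bin(180, 2/3) > 90) would also be above 0.9999.

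**Step 3: the two sentences on unblinding.** One places unblinding after the analysis is complete. The other gives, as a purpose of unblinding, completing the comparisons. If the comparisons remain to be completed, the analysis was not complete. If it was complete, group identity is needed only to name the arms in the results.

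**Step 4: a possible second route.** The Data analysis section plans correlations that use acupuncture sensation scores. Under Interventions, deqi is required at every point in the acupuncture arm and is not to be obtained in the sham arm. If these scores are collected in both arms, which the article does not say, they also point to the arm. The conclusion does not depend on this.

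**The case against.** The best defence is that analyst blinding matters little when the analysis is fixed in advance. The article defers further detail on added analyses to a statistical analysis plan, and that plan may already settle the choices named here. The primary outcome rests on what blinded patients record ("According to the headache diary, patients will be asked about the duration of headache"), and participant blinding is assessed with Bang's index. The full analysis set, not the per-protocol set, carries the primary analysis. The article never mentions masked labels, only role separation and late unblinding. All of this stands, and it limits the consequence. It does not make the statement about statisticians true. Role separation keeps the statistician away from treatment but not from the group sizes, and an analysis plan cannot change the fact that a 2:1 split shows which group is larger.

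A reader might also infer that evaluator blinding fails, because the Data management section says that each CRF "will be meticulously completed by the investigator based on the participant", the sources being hospital records and original observation notes. The documents do not support this. Nothing says that those records show points, deqi or arm, or that the evaluator reads them. The Discussion assigns different researchers to treatment, outcome assessment and analysis. CRF layout and lists of source documents are matters that a condensed article commonly leaves to the full protocol.

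What remains is a difference about who does what. Blinding says "Evaluators are responsible for collecting and analyzing the data unrelated to the treatment process". Data management has the investigator complete the CRF. Quality control gives the task to the trial's clinical participants. The treatment course section lists symptom assessment and CRF completion without naming who does them.

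**Conclusion.** The point holds for statisticians. The stated blinding until the analysis is complete cannot rest on withheld group identity, because the larger group is acupuncture with probability above 0.9999 under equal losses of 10% or 20%, and about 0.98 under an assumed 40% loss from acupuncture alone. This assumes that the analyst works with data carrying a group code, which a between-group analysis requires. The Blinding section also contradicts itself on whether comparisons are finished before unblinding.

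The choice of test by normality and per-protocol membership by compliance would therefore be made with the arms identifiable, unless the unseen analysis plan fixes them earlier. A reader might go further and infer a biased primary result. No such bias is shown or quantified, and the diary of a blinded patient is the least likely place for it. For evaluators, the finding is only that the sections on blinding, treatment course, data management and quality control differ on who completes the CRF.

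**What to change.** In the Blinding section, stop relying on withheld group identity to blind the statistician. State instead that three things are finalised before the real allocation is merged with the data:

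- the analysis plan, including the rule for choosing the test;
- membership of each analysis set, including what counts as good compliance;
- the analysis code, tested on a scrambled allocation.

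Until then the statistician's dataset should carry no real group column, coded or not. Remove the step that lets comparisons be completed after unblinding.

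Separately, reconcile the sections on blinding, treatment course, data management and quality control so that they agree on who completes the CRF.

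The cost is a wording amendment and an earlier deadline for the code. Sample size and allocation ratio are unchanged. Recruitment is scheduled to run to 31 December 2026, so on the article's own timetable there should be time to make the change before the analysis.

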### Interventions

The intervention measures will be in accordance with the Uniform Standard for Trial Reporting (19) and the Standard for Reporting Interventions in Clinical Trials of Acupuncture and Moxibustion (20).

#### Treatment group

##### Acupoint selection

Based on clinical experience and previous research (21–24), and by incorporating suggestions from consensus meetings with clinical experts, the following acupoints will be selected: Baihui (GV20), Yintang (GV24+), Sishencong (EX-HN1), Shenting (GV24), Benshen (GB13, bilateral), Shuigu (GB8, bilateral), Fengchi (GB20, bilateral), Neiguan (PC6, bilateral), and Taichong (LR3, bilateral) (Table 1 and Figure 3).

**Table 1 tab1:** Acupoints and description of acupoint locations.

Location of real acupoints used in the real acupuncture treatment group	
Acupoints	Location
Baihui [GV20]	On the head, 5 cun directly above the anterior hairline.
Yintang (GV24+)	On the head, in the depression at the midpoint of the inner ends of the eyebrows.
Sishencong (EX-HN1)	On the top of the head, 1 cun anterior, posterior, and lateral to Baihui, forming a total of four points.
Shenting (GV24)	On the head, 0.5 cun directly above the anterior hairline.
Benshen (GB13)	On the head, 0.5 cun above the anterior hairline, 3 cun lateral to the midline of the head.
Shuaigu (GB8)	On the head, 1.5 cun directly above the apex of the ear.
Fengchi (GB20)	On the posterior neck area, in the depression below the occipital bone, between the upper ends of the sternocleidomastoid and trapezius muscles.
Neiguan (PC6)	On the anterior forearm, 2 cun proximal to the wrist crease on the palmar side, between the palmaris longus tendon and the radial flexor carpi tendon.
Taichong (LR3)	On the dorsum of the foot, in the depression between the 1st and 2nd metatarsal bones, or where the pulse can be felt.

Location of sham acupoints used in the sham acupuncture control group	
Sham acupoints	Location
Sham acupoint (1)	On the inside of the elbow, at the midpoint of the line connecting the tip of the elbow and the armpit.
Sham acupoint (2)	On the ulnar side of the forearm, at the midpoint of the line connecting the medial wrist crease and the medial epicondyle of the humerus.
Sham acupoint (3)	At the anterior border of the arm, at the junction between the deltoid and biceps muscles.
Sham acupoint (4)	At the midpoint of the line connecting the deltoid muscle and the acromion.
Sham acupoint (5)	1–2 cm lateral to the Zusanli (ST 36) point, along the outer edge of the tibia.
Sham acupoint (6)	On the rectus femoris muscle, at the midpoint of the line connecting the anterior superior iliac spine and the lateral end of the patella, 2 cm medial.
Sham acupoint (7)	At the midpoint of the line connecting the Qiuxu (GB40) and Jiexi (ST41) points.
Sham acupoint (8)	Between the Sanjiao Meridian of Hand-Shaoyang and the Small Intestine Meridian of Hand-Taiyang, at the level of Waiguan (TE 5), pointing outward.
Sham acupoint (9)	0.5 cun below the hairline at the corner of the forehead, 4 cun lateral to the midline (below and in front of the Touwei (ST 8) point).

